**Amber**
If one or more of the amber criteria are met, this study will be considered likely feasible:50%-79% of the target sample recruited within 3 months60%-79% of participants remain in the DESI-Heart program50%-65% of participants completed the set goals delivered via the DESI-Heart programAttrition: 20.1%-35%CA will be considered moderately usable if the Bot Usability Scale score is between 51-69.

For each self-care component, the system will deliver culturally tailored instructions and demonstrations followed by questions to determine whether participants completed the activity, their experience, and if they had any concerns. Participants’ responses to these questions will be recorded and saved to the BuddyLink database, enabling the research team to review weekly and modify content as required. During this period, researchers will check in via telephone weekly with participants to address any technical support needs.

After participants complete the 8-week DESI-Heart program, researchers will assist them in completing the follow-up post-study questionnaires online via Zoom. These will include all the questionnaires administered at baseline, minus the demographic questions. Additionally, participants will complete the Bot Usability Scale to report their perceived usability of the DESI-Heart program [46]. During pretesting, we observed that participants will be able to complete the full set of pre- and post-study questionnaires, including instructions, response time, and short breaks, within approximately 50 minutes. This supports the feasibility of administering the selected outcome measures without placing excessive burden on participants. Upon completion of the pilot study, participants will be remunerated for their time and involvement in the study (Figure 3). Subsequently, participants will also participate in an exit interview to better understand their perceptions of the DESI-Heart program, their level of satisfaction, and acceptability.

**Figure 3 figure3:**
[figure not shown]
Overview of DESI-Heart study protocol. CVD: cardiovascular disease; DESI-Heart: Diaspora Engaged Self-Care Intervention and Heart.

### User Testing

Before the commencement of this study, the platform was user-tested by research team members and volunteers over 2 weeks on both iOS (Apple Inc) and Android (Google LLC) operating systems. Feedback from this testing informed revisions to notification texts (via text messages and emails), improvements to navigation, adjustments to the user interface, and resolution of technical issues.

### Outcome Measures

The feasibility of this study will be measured using recruitment rates, participant retention, completion of the prescribed self-care program, and attrition. Feasibility will be assessed using criteria outlined in Textbox 1, informed by previous studies [35,43-45] and a “traffic light” system [47], to ensure transparent and standardized progression to a definitive trial. Usability will be assessed by the Bot Usability Scale [46]. Participant scores will be cross-validated with system logs and study records capturing interaction history, which will be accessible through BuddyLink. The usability of the DESI-Heart program is defined as a score of 70 and above, which corresponds to a percentile of 70%, indicating high perceived usability [46].

The secondary outcomes include changes (from baseline to 8 weeks) in participants’ self-care behaviors and quality of life as reported above (Table 1).

**Table 1 table1:** Baseline and follow-up measures.

Assessment or procedure		Screening	Stage 1 (1 week)	Stage 2 (8 weeks)
**Procedures**				
	Informed consent	✓	✓	✓
	Demographic information	✓	✓	✓
	Medication Adherence Report Scale-10 [39]		✓	✓
	Godin Leisure-Time Exercise Questionnaire [40]		✓	✓
	Cardio-Med Food Frequency Survey Tool [41]		✓	✓
	Self-Care Inventory (SCI) [42]		✓	✓
**Assessments**				
	World Health Organization Quality of Life (WHOQOL) [48]		✓	✓
	Chatbot Usability Scale [46]			✓

### Data Analysis

For the primary outcomes (recruitment, retention, program completion, attrition, and usability), the analysis will focus on reporting the observed frequencies and rates. For secondary outcomes, changes in quantitative measures between baseline and 8-week follow-up will be analyzed using paired-sample *t* tests (2-tailed). Analyses will be based on the normality of the data, and if parametric assumptions are not met, data transformation will be considered to better satisfy these assumptions. All analyses will be conducted using Stata (Version SE V.17.0; StataCorp). Data will be stored in the Qualtrics secure firewall-protected server hosted by Deakin University. Subsequently, the data will be transferred to a Deakin-managed Syncplicity server, and the data will be permanently deleted from Qualtrics.

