To address this gap in culturally appropriate CA interventions, we have co-designed a culturally tailored CA intervention (Diaspora Engaged Self-Care Intervention and Heart [DESI-Heart]) to support self-care among individuals with CVD from the Indian diaspora in Australia. DESI-Heart integrates cultural elements specific to Indian communities—including language preferences, traditional health practices, and culturally congruent communication styles. In this protocol paper, we present a comprehensive overview of the co-designed DESI-Heart program, detailing its design and development process guided by established cultural adaptation frameworks. We also outline the planned pilot study to evaluate its feasibility and usability, and potential impact on self-care outcomes.

The primary aim was to evaluate the feasibility and usability of a co-designed culturally tailored CA (DESI-Heart) in supporting self-care management among Indian diaspora populations with CVDs in Australia over an 8-week intervention period.

The primary objectives were (1) to determine participant recruitment rates, retention rates, and adherence to the DESI-Heart program; and (2) to assess the usability of the DESI-Heart program using validated measures of the Bot Usability Scale.

The secondary objective was to evaluate preliminary effects of the DESI-Heart program on changes from baseline to 8 weeks in CVD self-care behaviors and quality of life.

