### Study Overview

An 8-week single-arm prepost pilot trial will be conducted. Participants will receive a personalized DESI-Heart program, which includes the 4 core modules described above, delivered via the CA at their preferred time of day. All assessments will be administered through web-based questionnaires at baseline and at the end of the 8-week program.

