### Sample Size

Preliminary calculations using G-power indicated that a total of 28 participants will be sufficient to allow an (estimated) proportion of 80% for recruitment to be estimated with a 95% CI of ±15%.

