**Green**
If one or more of the green criteria are met, this study will be considered feasible in its current form:At least ≥80% of the target sample size is recruited and enrolled in the Diaspora Engaged Self-Care Intervention and Heart (DESI-Heart) program within 3 months [35]At least ≥80% of participants remain in the DESI-Heart program [43]At least ≥66% of participants completed the set goals delivered via the DESI-Heart program [44]Attrition ≤20% [45]Conversational agent (CA) will be considered usable if the Bot Usability Scale score is >70 [46].

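### The 8-week questionnaires are described as following programme completion and are analysed by paired t tests, so read literally the secondary change is that of people with 8-week data only

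*Protocol article*

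**What the plan says.** The secondary objective, at the end of the Introduction, is to "evaluate preliminary effects of the DESI-Heart program on changes from baseline to 8 weeks in CVD self-care behaviors and quality of life". It names a time span but no analysis population.

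The timing of the follow-up assessment is given in different ways:

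- Procedure: "After participants complete the 8-week DESI-Heart program, researchers will assist them in completing the follow-up post-study questionnaires online via Zoom". This is the only account of how follow-up is carried out.
- Study Overview: "All assessments will be administered through web-based questionnaires at baseline and at the end of the 8-week program".
- Table 1: the follow-up column is labelled by time, at 8 weeks.

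Data Analysis fixes the method for the secondary outcomes: "changes in quantitative measures between baseline and 8-week follow-up will be analyzed using paired-sample" t tests, two-tailed, with transformation considered if parametric assumptions fail.

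Textbox 1 accepts attrition of up to 20% as Green and from 20.1% to 35% as Amber. Its retention indicator refers to remaining in the programme under Green and Amber, but to remaining in the study at 8 weeks under Red.

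**The concern.** A paired t test needs both values from each person. Anyone without an 8-week value drops out of the analysis, and their observed baseline goes with them. If the questionnaires are offered only to people who complete the programme, everyone who stops early is lost in this way. The result then describes change among those who stayed.

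That matters if leaving is related to self-care or to benefit. The Introduction says that sustained engagement with digital interventions is hard, and cites health and digital literacy, privacy worries and complex interfaces. It is plausible, though the article does not show it, that the same barriers go with poorer self-care or smaller gains. At stake is how the preliminary changes in self-care and quality of life can be read.

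The protocol also does not separate leaving the programme from leaving the study, as the changing wording of the retention indicator shows. Site staff could therefore reasonably act on either reading of Procedure.

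**Working it through.** **1. The plan's own figure.** Sample Size gives 28 for a proportion of 80% with a 95% CI of ±15 points. The usual precision formula is n = z²p(1−p)/d² = 1.96² × 0.80 × 0.20 / 0.15² = 27.3, rounded up to 28. The figure reproduces. It concerns recruitment and says nothing about the precision of the secondary changes.

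**2. Pairs left at the attrition limits (Textbox 1, N = 28).**

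- Green: 0.20 × 28 = 5.6, so at most 5 leave (17.9%) and 23 pairs remain.
- Amber: 0.35 × 28 = 9.8, so at most 9 leave (32.1%) and 19 pairs remain.

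This takes leavers to be people without 8-week data.

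**3. Effect on the estimated change.** Let C be the mean change in people with 8-week data, rC the mean change in leavers, and a the share leaving. The all-enrolled change is C(1 − a(1 − r)), so the reported change is 1/(1 − a(1 − r)) times the all-enrolled change. The documents give no value for r, so the range is shown.

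| r (assumed) | 5 of 28 leave | 9 of 28 leave |
|---|---|---|
| 0 (leavers do not change) | 28/23 = 1.22 | 28/19 = 1.47 |
| 0.25 | 1.15 | 1.32 |
| 0.5 | 1.10 | 1.19 |
| 0.75 | 1.05 | 1.09 |
| 1 (same change as stayers) | 1.00 | 1.00 |

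**4. Dropout that depends on baseline.** Assumptions, none from the documents: baseline standard normal, follow-up = 0.40 + 0.5 × baseline + noise, so the true change is 0.40 SD and the correlation 0.5; odds of dropout multiplied or divided by e per SD of baseline. The expected paired change is 0.40 − 0.5m, where m is the mean baseline of those who stay.

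- 20% attrition: m = ±0.17, so the paired change is about 0.31 if low-baseline people leave and 0.49 if high-baseline people leave.
- 35% attrition: m = ±0.29, giving about 0.25 or 0.55.

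In simulation (n = 28, 8,000 replicates) a likelihood-type estimate using all baselines gave about 0.40 in every case, with a standard error 1–4% larger than the paired analysis.

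**5. What the model cannot do.** Suppose instead that leavers have zero change, dropout is unrelated to baseline, and stayers change by 0.40. The true all-enrolled change is 0.40 × 23/28 = 0.33 with 5 leavers, or 0.40 × 19/28 = 0.27 with 9. In simulation the paired and the likelihood analyses both gave 0.40. The model corrects only missingness explained by baseline; only data from the leavers can settle the rest.

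**The case against.** The strongest reply is that the Procedure sentence may simply mean the end of week 8. Study Overview, Table 1 and the secondary objective all set the assessment by time, and nothing says that people who stop will not be contacted. Someone who stops using the conversational agent but answers at week 8 would be in the paired analysis. This stands. A reader might infer that the plan excludes leavers by rule, but the documents support only an ambiguity whose literal reading has that effect.

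It can also be said that the objective names no population, so no stated target is contradicted; that missing-data handling may sit in an analysis plan that is not shown; and that a paired t test is not in itself an error in a single-arm pilot. These points are fair. However, whom to ask for follow-up data is a matter of procedure, which this article does describe, and the test it names has the complete-pairs property whatever is added elsewhere.

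A reader might further infer that an inflated change would make the next trial too small. The Discussion does not support this. It says the pilot will inform eligibility, recruitment, agent features and delivery preferences for a powered trial, not that the pre-post change will size it, and the Conclusions foresee comparator groups. The Discussion also disclaims definitive efficacy evaluation, though because of sample size and the single arm rather than selective loss.

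**Conclusion.** The point holds in a limited form. The statements on when and from whom follow-up is sought do not agree, and under the literal reading of Procedure the paired t test yields the change only in people with 8-week data, meaning those with a questionnaire and not those who met the goal-completion criterion.

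At the plan's own limits that is 23 or 19 of 28 people. The factors of 1.22 and 1.47 are upper values under the assumption that leavers do not change; they would be larger only if leavers got worse, and they fall to 1.00 if leavers change as stayers do. With baseline-related dropout the error can go in either direction, so the documents establish neither the size nor the sign of any bias. The outcome is secondary and preliminary. The correction is worth making because it is cheap, not because the primary feasibility results depend on it.

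**What to change.** 1. **Procedure (the main remedy).** Reconcile the timing statements by saying that the 8-week questionnaires are sought at 8 weeks after programme start from every enrolled participant, whether or not they still use the programme, unless consent is withdrawn.
2. **Data Analysis.** Name the analysis population. Estimate the change with a likelihood-based repeated-measures model for the two visits (visit as fixed effect, unstructured covariance) that includes everyone with a baseline. Report the mean change with its 95% CI and the number of complete pairs, and state that the model corrects only missingness explained by baseline. With no missing data the point estimate equals the mean paired difference.
3. **Sensitivity analysis.** Add a result in which people without an 8-week value are given zero change, labelled as an assumption.

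The cost is one sentence in Procedure, a few lines of Stata, and follow-up of about 5 to 9 more people at the attrition limits. The standard error was 1–4% larger in simulation, and the reported change may be less favourable. The Results section says that analysis starts once follow-up is finalised, so items 2 and 3 can be fixed beforehand. If follow-up has already closed, item 1 becomes a statement of who was actually approached.

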### Ethical Considerations

This study received ethics approval from the Royal Melbourne Hospital Human Research Ethics Committee (HREC/76317/MH-2021) for all procedures involving people living with CVDs. For this project, the platform operates as a dedicated instance with encrypted data storage, strict role-based access, and no local software requirements beyond a modern web browser. Personal identifiers or sensitive health data will not be collected; researchers can link participants only through nonidentifiable IDs, ensuring anonymity. Voice recordings are not stored, and transcriptions or logs can be deleted at any time upon request. End users retain full rights to access, correct, or delete their data via the platform’s privacy portal. Messages and email links sent to participants are delivered via the BuddyLink platform solely to provide access to the intervention. Upon completion of this study, participants’ mobile numbers and email addresses will be permanently deleted from the BuddyLink platform. The shared subscription calendar is independently hosted via Google Calendar. It will be sent to participants for download into their own calendars, and no information will be transferred to or shared via BuddyLink.

Before enrollment, all participants will be provided with a plain language statement outlining this study’s purpose, procedures, potential risks and benefits, the use of CAs and optional AI-enabled features, and how their data will be managed. Participants will be able to ask questions and receive clarification from the research team before deciding to participate. Informed consent will be obtained through an online consent form. Each participant will be provided with a AUD $100 (US $66.50) Woolworths Essentials gift card as compensation upon completion of the study. The datasets generated and analyzed during this study will be securely stored on the Deakin-managed Syncplicity server. These data will not be publicly available but may be made accessible by the primary investigator upon reasonable request and with approval from the Royal Melbourne Hospital Human Research Ethics Committee. To disseminate the findings, a summary of the results will be emailed to participants and presented to research teams. Findings will also be shared with the scientific community through peer-reviewed publications and conference presentations.

## Results

Recruitment for the pilot trial was scheduled to begin in June 2025 and concluded by September 2025. Participant follow-up will be completed by the end of December 2025. All 28 participants have now been recruited, and data analysis will be conducted once follow-up is finalized. Upon completion of data analysis, the findings from the pilot study will be submitted for publication.

## Discussion

### Principal Findings

This article outlines the protocol for pilot testing for the feasibility and usability of the DESI-Heart program, a systematically co-designed, culturally tailored CA designed specifically to support self-care management among Indian diaspora populations with CVDs in Australia. This innovative digital health solution addresses a critical gap in culturally appropriate self-care support for people living with CVDs belonging to different CALD backgrounds.

Through the advancement of natural language processing, AI, voice recognition, and large language models, CAs have become increasingly integrated into health care and health management [49]. These technologies offer scalable and cost-effective solutions that can provide medical support anytime through smartphones, mobile apps, or web-based platforms [50]. Evidence suggests that CA-based interventions can significantly support both patients and clinicians by assisting with specific tasks and processes [44]. Multiple CA-based interventions have demonstrated improvements in enhancing self-care behaviors, such as increased physical activity, healthier dietary habits, and better medication adherence [51]. However, much of the existing research and development has focused on the general population, with limited attention given to CA systems tailored for CALD communities [52]. Cultural beliefs and practices are deeply incorporated into everyday lives and affect how individuals approach self-care [22]. Due to these cultural differences, individuals from CALD communities often face additional challenges in navigating self-care. Their native cultural beliefs and practices may differ significantly from those of the host culture, leading to confusion, strain, or reduced engagement with mainstream health services [53,54]. This cultural disconnect can ultimately contribute to health disparities and poorer CVD outcomes among immigrant populations.

To address this gap, we applied DDM and EVM as cultural adaptation frameworks to guide the development and design of a culturally appropriate, CA-based CVD self-care management program. This methodologically rigorous approach ensured that cultural considerations were central rather than peripheral to the intervention design process. Through co-design workshops with end users, we identified key features to enhance the program’s cultural relevance, gathered ideas to improve cultural appropriateness, and received suggestions to increase participant engagement with the culturally appropriate self-care intervention.

DESI-Heart program—includes 4 carefully designed core modules (medication reminders, physical activity support, dietary guidance, and stress management through meditation). The content has been specifically developed to resonate with the Indian community by incorporating culturally relevant examples, familiar language patterns, and delivery styles that align with cultural norms, in order to foster engagement and enhance content appropriateness. This program also provides access to DESI-Heart in multiple Indian languages, increasing the accessibility of support to those who speak languages other than English.

By providing culturally and linguistically appropriate self-care information and support, the DESI-Heart program aims to increase engagement in self-care behaviors that are culturally meaningful and sustainable. The CA used in this study has been designed to be user-friendly across varying levels of digital literacy, addressing a known barrier to digital health adoption among older adults and immigrant populations. It incorporates advanced voice recognition technology capable of understanding diverse accents, dialects, and several Indian languages, ensuring accessibility for a broader range of participants. Participants can interact with the CA either through voice commands or touch, allowing flexible access to care based on their preference. This makes DESI-Heart a more inclusive and accessible CA-delivered CVD self-care management tool, particularly when compared to existing CA interventions that often lack cultural tailoring [15,52]. Moreover, DESI-Heart supports participants in integrating their own cultural beliefs with key aspects of the host country’s health care norms. This dual approach not only enhances the effectiveness of the intervention for CALD communities but also positions DESI-Heart as a model for culturally responsive digital health support.

Despite its innovative features, several important limitations of the DESI-Heart program warrant acknowledgment. While the program was designed based on general Indian cultural values, it did not fully account for the regional and linguistic diversity that exists within the Indian community, particularly the differences between northern and southern cultural practices. These regional variations can significantly influence health-related behaviors, beliefs, and preferences [55], which may affect the program’s relevance and effectiveness for some participants. Additionally, as a pilot feasibility study with a relatively small sample size and single-arm design, this investigation cannot definitively evaluate efficacy outcomes. The current inclusion criteria limit the program’s inclusivity, as participants with severe conditions or those residing in care facilities were not included, which may affect the interpretation and applicability of the findings.

Findings from this pilot study will offer critical insights to guide the design of a future, fully powered efficacy trial. These will include broader eligibility criteria, refined recruitment strategies, enhancements to CA-related features and functions to improve engagement, and tailored delivery preferences for specific participant subgroups, thereby strengthening the generalizability of the results. Future studies could also focus on specific ethnic groups with similar cultural and linguistic backgrounds to provide more targeted and appropriate support. Additionally, trial findings may guide the implementation and adaptation of this approach for CVD management services within other CALD communities, supporting their specific cultural needs and requirements while making health care more accessible, appropriate, and equitable. The knowledge generated may also contribute to a broader understanding of how to effectively incorporate cultural elements into digital health interventions.

